#### Placement in a matching competitive workplace

The participant will be supported in the search for a suitable workplace by one of the three rehabilitation agencies that participate in the study. Intervention group participants will be equally assigned to the participating agencies.

After receiving the written action plan for RTW, the RTW coordinator will contact the case manager of the assigned rehabilitation agency and will inform the case manager about necessary preconditions for RTW. The rehabilitation agency will receive a copy of the action plan for RTW.

Within four weeks, the agency has to offer at least two suitable workplaces, with a contract period of at least three months, matching with the formulated consensus-based action plan for RTW and taking into account the participant’s preferences. The employment contract has to result in at least 50 percent of the earnings of the participant’s last job. Alternatively, placement for a maximum of three months with ongoing sickness benefit is possible, but only when after these three months the employment contract meets the requirements mentioned above. In that case, there should be an intention to offer the participant a (temporary) employment contract. A financial reward will be given by the SSA to the rehabilitation agency for the job hunting and/or for the actual placement in a matching workplace. The participant will be actively involved in the job searching.

The case manager of the rehabilitation agency is responsible for proper guidance of the participant. If required, the case manager will visit the workplace to instruct and advise the participant. And, if necessary, the supervisor and/or colleagues at the workplace can be informed by the case manager about how to guide the participant at the workplace.

#### Evaluation

Four weeks after the start of the job search by the rehabilitation agency, the RTW coordinator will contact the participant and the case manager of the agency by telephone to inform whether placement in a workplace has been successful. The RTW action plan will be evaluated and, if necessary, the action plan will be adapted to new circumstances. The RTW coordinator summarizes findings in a final report.

In case the assigned rehabilitation agency has not been able to offer a suitable workplace, the other two rehabilitation agencies participating in the project will also get the opportunity to search for suitable vacancies.

Six weeks and three months after placement in a workplace, the case manager of the rehabilitation agency will evaluate the program with the participant, and will send a report with a summary of the most important findings to the RTW coordinator of the SSA.

#### Training of the professionals

Instruction will be given to all intervention teams by the researchers. At each participating SSA office instruction takes place by means of a presentation and role plays during one session of approximately three hours. In the beginning of this session all professionals will receive a syllabus with detailed information about the program, the protocol, practical summaries and schemes and practice material. A few months after the first participants have enrolled in the intervention, the researchers will visit every participating intervention team for a follow-up session to evaluate the first cases and to discuss difficulties in applying the protocol in daily practice.

### Use of co-interventions

Co-interventions cannot be avoided. It is possible that the study participants will receive other interventions. In both the intervention and control group received co-interventions will be monitored in each follow-up measurement.

### Outcomes

#### Effect evaluation

The primary outcome measure is the duration until first sustainable RTW in competitive employment. This is defined as the duration in calendar days from the day of enrolment in the study until first sustainable RTW in a competitive job for at least 28 consecutive calendar days without partial or full recurrence of sickness absence. In line with Crowther et al. [25], competitive employment is defined as a full or part-time position held by the worker in a regular work setting, for which payment is received at the market rate.

According to the Dutch Sickness Benefit Act, recurrence of an accepted sickness benefit claim within 28 calendar days after ending of the previous benefit is considered as belonging to the preceding sickness benefit period, on condition that it is due to the same (or related) disorder. Although for sick-listed workers without a permanent employment contract ending of the sickness benefit not automatically results in RTW, it was chosen to mark RTW as sustainable only when the participant returned to work for at least these 28 calendar days.

RTW data, i.e. work resumption in regular (paid) work, are registered continuously by the Dutch SSA and will be collected from the SSA database after twelve months follow-up.

In addition, with a self-administered questionnaire the participant will be asked whether he or she has worked in (un)paid labour in the last three months. If the participant did RTW, he or she will be asked to specify the period in which RTW has taken place and the average working hours per week.

Secondary outcome measures are:

– *RTW in any type of work*

 In addition to the primary outcome measure, the duration until first RTW in any type of work will be measured, i.e. paid work, unpaid work and work with ongoing supportive benefit.

– *Duration of the sickness benefit period*

 For workers without a permanent employment contract, it is possible that the sickness benefit ends, before full RTW is achieved. The worker can be recovered from illness or functional limitations (assessed with regard to last or previous work) without actual RTW, because the worker has no workplace to return to. Therefore, in line with Vermeulen and colleagues, the duration of the sickness benefit period will be assessed as well. This is defined as the duration of the sickness benefit from the day of enrolment until ending of the sickness benefit for at least 28 consecutive calendar days [21]. Additionally, the total number of days of sickness benefit during follow-up will be calculated. Awarded sickness benefit claims during follow-up are only included in the calculation when the participant is sick-listed due to the same (or related) mental disorder [21]. Data on sickness benefit will be collected from the SSA database and by self-report of the participants.

– *Work status*

 Work status is defined as the average number of hours worked per week during the one-year follow-up. In addition to a self-administered questionnaire, the SSA database will be used to collect this information.

– *Severity of mental disorder symptoms*

 Severity of mental disorder symptoms will be assessed using the Four-Dimensional Symptom Questionnaire (4DSQ) [34].

– *Perceived general health status*

 Using the Dutch translation of the SF-36 [35] perceived general health status will be measured.

– *Quality of life*

 Quality of life will be measured using the Dutch translation of the Euroquol questionnaire [36].

– *Attitude, Social influence, and self-Efficacy (ASE)*

 For the development of earlier participatory RTW programs the Attitude-Social influence-self-Efficacy (ASE) model was used as an underlying theoretical framework [37,38]. In these studies the ASE constructs were assessed using a questionnaire developed by Van Oostrom and colleagues [39]. In this study we will make use of the same questionnaire.

– *Work limitations*

 Work limitations will be measured with the Dutch translation of the Work Limitations Questionnaire (WLQ) [40].

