### Data collection

The baseline questionnaire will be filled in during the intake appointment at the SSA, after signing informed consent. All other questionnaires will be filled in online, unless the participant prefers to receive a hard copy by postal mail.

Participants will receive questionnaires at baseline and after three, six, nine and twelve months.

In case questionnaires will not be returned within two weeks after the questionnaire is sent, the researcher will contact the participant by telephone to inform whether the participant has been able to complete the questionnaire and to ask the participant, if possible, to complete the questionnaire timely. In case the participant returns the questionnaire, but the received questionnaire is incomplete, the researcher will also contact the participant by telephone. The remaining questions will be repeated by the researcher, so that the questionnaire can be completed by the participant.

In addition to the questionnaires, after one year follow-up data regarding RTW, sickness absence, diagnosis, OHC interventions and investments made by the SSA will be obtained from the SSA database and the medical file of the worker at the SSA. These data will be checked with the self-reported information in the questionnaires.

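### The three-month look-back equals the gap between questionnaires, so a missed or late wave can lose a short unpaid first return for the secondary outcome of return to any work (minor)

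*Protocol article*

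**What the plan says.** In the Protocol article, Outcomes (Effect evaluation), the self-report item on work is described thus: "the participant will be asked whether he or she has worked in (un)paid labour in the last three months". Participants who did return are followed up in the same item: "he or she will be asked to specify the period in which RTW has taken place and the average working hours per week".

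Data collection sets the schedule: "Participants will receive questionnaires at baseline and after three, six, nine and twelve months". It also provides for late forms: "In case questionnaires will not be returned within two weeks after the questionnaire is sent, the researcher will contact the participant by telephone". Incomplete forms are completed by telephone. No question is described that reaches back past a missed or late wave.

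On the register, Effect evaluation says: "RTW data, i.e. work resumption in regular (paid) work, are registered continuously by the Dutch SSA". These data are collected after twelve months and, under Data collection, checked against self-report.

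The first secondary outcome is wider than the register as described: "the duration until first RTW in any type of work will be measured, i.e. paid work, unpaid work and work with ongoing supportive benefit". The 28-day minimum of the primary outcome is not stated for it, so a short spell counts.

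**The concern.** A look-back equal to the interval between waves covers the whole year only if every questionnaire is answered on schedule. The plan foresees that some will not be, since it has a telephone procedure for forms outstanding after two weeks. That contact helps to get the form completed, but nothing described lengthens the period the form asks about.

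For regular paid work the register stands behind the questionnaire. For unpaid work, self-report is the only source described. Checking the two sources against each other cannot recover a spell that neither recorded. If such a spell was the participant's first return of any kind, the time to first return to any work is recorded too long, or the participant is counted as not having returned. Analysis cannot repair this afterwards.

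**Working it through.** The article states no coverage figure to reproduce, so this is a day count.

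**Inputs.** Look-back of three months, taken as 13 weeks = 91 days (Effect evaluation). Waves at 3, 6, 9 and 12 months, taken as days 91, 182, 273 and 364 (Data collection). Telephone contact once a form is two weeks outstanding (Data collection). Assumption for the late-wave case only: the window counts back from the day of completion.

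**All waves on time.** Four windows of 91 days: 4 × 91 = 364, so 0 of 364 days are uncovered. There is no overlap to absorb any slippage.

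**One wave missed, the next completed on time.** Uncovered = 364 − 3 × 91 = 91 days, and 91/364 = 25% of follow-up. This result does not depend on whether the window is anchored at completion or at the due date.

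**One wave late.** Uncovered = (days since the previous completion) − 91. For month 3 answered on day 91 and month 6 on day 203: 203 − 91 = 112, and 112 − 91 = 21 days. More generally, one wave 2, 3 or 4 weeks late leaves 14, 21 or 28 days uncovered. If all four are two weeks late, the total is still 14 days, at the start of follow-up, because lateness matters only relative to the previous wave.

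**What is lost inside a gap, by type of work.**

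| Type of work | Other source described | Exposed? |
|---|---|---|
| Regular paid | SSA register, continuous | Largely no |
| With ongoing benefit | Possibly visible in SSA benefit data and files | Uncertain |
| Unpaid, still running when the next window opens | The item on the period of return can give its start | Probably recoverable |
| Unpaid, starting and ending inside the gap | None | Yes |

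**How many participants have a gap.** The article gives no rate of skipped waves. Purely as an assumption, if each of the four waves is missed independently with probability 5%, 10% or 20%, the share missing at least one is 1 − 0.95⁴ = 19%, 1 − 0.90⁴ = 34% or 1 − 0.80⁴ = 59%. This is the share with a gap from a missed wave, not the share with a lost return. The latter also requires a first return that is unpaid and confined to the gap, and the article gives no input for that.

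**The case against.** The strongest objection is that the questionnaire is not shown. The article paraphrases one item in one sentence, and the real form may anchor the window at the due date or include a catch-up question. That stands as a limit: the late-wave gap rests on the completion-date assumption, and the absence of catch-up is read from the description alone. The missed-wave gap follows from the look-back and schedule as stated. It is also an inference, though a natural one, that a register described as holding regular paid work lacks unpaid work.

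A short fixed recall period is also defensible, because it limits recall error. That is true, and the remedy gives some of it up, but only for participants who were late or missed a wave.

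Several stronger readings are tempting and are not supported:

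- *A reader might infer a size* by applying the hazard ratio of 2.0 and the two-thirds return share from Sample size to the months in a gap. Those inputs describe first sustainable return in a competitive job, which the register covers, so they do not measure unpaid first returns.
- *A reader might infer bias between arms*, because the arm returning earlier would have more first returns in an early gap. That carries the competitive-job hazard ratio over to unpaid work, for which the article gives no basis.
- *A reader might take the expected 20% loss to follow-up as the rate of skipped waves.* It is not a rate of intermittent missingness, and someone who never answers again is not helped by a longer look-back.
- *A reader might infer that running spells are dated to the start of the window.* The item asks participants to specify the period, so the true start can be given.
- *A reader might extend the point to hours worked.* The definition reads: "Work status is defined as the average number of hours worked per week during the one-year follow-up". It also draws on the SSA database and does not say that unpaid hours count.

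**Conclusion.** The point holds as a minor one. The look-back and the schedule, as stated, leave no margin: a missed month-3, 6 or 9 wave followed by a completed one leaves about 91 days unasked, and a late wave leaves roughly as many days as it is late relative to the previous one, if the window runs back from completion. The consequence is confined mainly to the unpaid component of one secondary outcome, duration until first return to any type of work, and there to spells that begin and end inside a gap. The direction for an affected participant is clear (too late or missed). The number affected, and whether the arms differ, cannot be judged from the article. The primary outcome is not materially threatened by this.

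**What to change.** Replace the fixed three-month reference with a question about all work since the last completed questionnaire, showing its pre-filled date, or since enrolment if no follow-up questionnaire has been completed. Ask for the start and end date of each paid, unpaid or benefit-supported period of work.

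With this change, a late wave, or a missed month-3, 6 or 9 wave followed by a completed one, leaves 0 days unasked. It does not help participants who never return, and a missed month-12 wave would still leave 91 days uncovered.

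The cost is one wording change and a pre-filled date in the online and postal forms. Recall is longer, and so somewhat less exact, for participants who missed a wave. The change has to be made before the follow-up questionnaires go out.

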### Prognostic measures

Demographic characteristics, information regarding last work, type of worker before reporting sick and reason for reporting sick will be assessed with a self-administered questionnaire at baseline.

At the same time, the way health complaints influence vocational rehabilitation will be assessed. This will be measured with questions belonging to the subscale ‘Fear-avoidance beliefs’ of the Dutch Work Reintegration Questionnaire (WRQ) [41,42].

During follow-up, in case full RTW is not (yet) achieved, RTW expectations are measured. With a self-administered questionnaire, participants will be asked to indicate the period within they think it is possible to achieve full RTW (in ‘own’ work or other).

In addition, in each questionnaire participants will be asked whether they received RTW coaching by the SSA and whether they were treated for their health complaints. In case the participant indicates that he or she received RTW coaching by the SSA, questions will be asked about efforts made by the SSA to reintegrate the participant, e.g. investments in education or training and contracting a rehabilitation agency. The participant will be asked to rate the efforts of the SSA on a scale of one to ten. Also, when applicable, the participant will be asked to describe the treatment for his/her health complaints.

### Economic evaluation

Direct and indirect costs will be measured to conduct an economic analysis from the social insurer’s perspective and the societal perspective.

Costs for health care utilization, OHC and investments in vocational rehabilitation support made by the SSA are considered as direct costs. Examples of investments made by the SSA are training or education, interventions aimed at health promotion and contracting a rehabilitation agency to search for a workplace.

Indirect costs are related to paid sickness benefits. In case an employee becomes sick-listed, loss of productivity is normally considered to be part of the indirect costs. However, because sick-listed temporary agency workers, unemployed workers and workers with an expired fixed-term employment contract no longer have an employment contract, loss of productivity does not result in indirect costs [23]. Unemployed workers and workers whose employment contract ended during sickness absence have no workplace (anymore), which means there is no loss of productivity. The sick-listed temporary agency worker will, in case of sick-listing, be replaced with a healthy worker, which results in no productivity loss for the company concerned.

Data on paid sickness benefits and costs for investments made by the SSA will be collected from the SSA database and the worker’s files after one year follow-up. Data on OHC by the SSA professionals, i.e. number of consults during follow-up and type of OHC professional, will be collected from the SSA database and the medical files. Health care utilization will be measured by the Trimbos/iMTA questionnaire for Costs associated with Psychiatric Illness (Tic-P) [43]. The Tic-P is developed to measure health care utilization of people with mental illnesses. It quantifies the number of visits to different health care providers. Prices for different health care services suggested in guidelines for economic evaluation in the Netherlands will be used to value the health care consumption [44].

### Process evaluation

Based on the framework of Steckler and Linnan a process evaluation will be conducted [45]. The aim of the process evaluation is to determine the compliance with the intervention protocol, the feasibility of the participatory supportive RTW program and to assess satisfaction with the OHC guidance in accordance to this program. Three months after the participant has been assigned to the intervention group, the participant, the OHC professionals of the intervention team and the case manager of the rehabilitation agency will all receive a questionnaire. The OHC professionals and the case manager of the rehabilitation agency will be asked whether the intervention was applied according to the protocol. Additionally, they will be asked about applicability, compliance, satisfaction and barriers regarding implementation of the participatory supportive RTW program. Also the participants will be asked about their satisfaction with the participatory supportive RTW program. These questions are based on the Patients Satisfaction with Occupational Health Services Questionnaire (PSOHSQ) [46] and will be included in the three months questionnaire.

During the participatory supportive RTW program, standardized schemes will be used by the OHC professionals to describe identified barriers for RTW, the formulated solutions, the resulting consensus-based action plan for RTW and a final report. These schemes will be used to collect additional data about the implementation of the participatory supportive RTW program.

An overview of the measures and measurement instruments, including a time path for all measurements, is presented in Table 1.

**Table 1 T1:** Overview of measurements and time path

**Measurement**			** Time path**		
	**Baseline (T0)**	**3 months (T1)**	**6 months (T2)**	**9 months (T3)**	**12 months (T4)**
*Prognostic measures:*					
Demographic characteristics (e.g. age, gender)	X				
Last work (shifts, hours)	X				
Type of worker before reporting sick	X				
Reason reporting sick	X	X			
Interference of complaints (WRQ)	X				
RTW expectations	X	X	X	X	X
RTW interventions	X	X	X	X	X
Satisfaction with OHC	X	X	X	X	X
Health care interventions	X	X	X	X	X
*Primary outcome measure:*					
Duration until first sustainable RTW	X	X	X	X	X
*Secondary outcome measures:*					
Duration of sickness benefit	X	X	X	X	X
Work status	X	X	X	X	X
Severity of mental disorder symptoms (4SDQ)	X		X		X
Perceived general health status (SF-36)	X		X		X
Quality of life (Euroqol)	X		X		X
ASE determinants (ASE questionnaire)	X		X		X
Work limitations (WLQ)			X		X
Health care utilization (Tic-P)	X	X	X	X	X
Patient satisfaction* (PSOHSQ)		X			

*Patient satisfaction with occupational health care services is only measured in the intervention group (as part of the process evaluation).

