#### Guidance by the RTW coordinator and insurance physician

Within two weeks after the intake appointment at the SSA, the participatory supportive RTW program will start with an examination of the sickness benefit claim by the RTW coordinator and a medical assessment by the insurance physician conform usual OHC. In addition, the participant will receive a take-home assignment from the RTW coordinator. He or she will be asked to list obstacles for RTW as a preparation for the first meeting with the labour expert. Obstacles can be both work related or non-work related.

A strong cooperation and communication between the insurance physician, the GP and mental health care specialists are required. Therefore, the insurance physician will contact the caregivers of the participant right after the first medical assessment by telephone to make sure that the participant is given no conflicting advice and to agree upon treatment and RTW options.

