#### Economic evaluation

Cost-effectiveness will be assessed from both the social insurer’s perspective and the societal perspective by dividing the incremental costs by the incremental effects. The incremental cost-effectiveness ratio (ICER) represents the additional costs needed to gain one extra unit of effect in the intervention group compared to the control group. Cost-utility will be measured by dividing the differences in total costs by the difference in QALYs between the two groups.

A cost-benefit analysis will be conducted from the societal perspective. The net monetary benefit will be calculated by subtracting the difference in total costs between the two groups from the differences in productivity gain. Return on investment will be measured by dividing the incremental benefit (gain minus costs) by the incremental costs of the investment.

Bootstrapping will be used to estimate uncertainty surrounding the incremental costs. Confidence intervals (95%) around the mean costs differences will be computed by bias corrected and accelerated bootstrapping.

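### The Euroqol is taken only at 0, 6 and 12 months although questionnaires also go out at 3 and 9 months, so the QALY difference may carry an avoidable interpolation error of unknown direction

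*Protocol article*

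**What the plan says.** - **Instrument.** Outcomes, Effect evaluation: "Quality of life will be measured using the Dutch translation of the Euroquol questionnaire".
- **Schedule.** In Table 1 the row "Quality of life (Euroqol") is marked at T0, T2 and T4 (baseline, 6 and 12 months) and is blank at T1 and T3 (3 and 9 months).
- **Other possible source of utilities.** The row "Perceived general health status (SF-36") has the same three marks, so it cannot fill the gap.
- **Mailings.** Data collection: "Participants will receive questionnaires at baseline and after three, six, nine and twelve months". The row "Health care utilization (Tic-P") is marked at all five times.
- **Use.** Statistical analysis, Economic evaluation: "Cost-utility will be measured by dividing the differences in total costs by the difference in QALYs between the two groups". The article does not say how Euroqol readings become QALYs.
- **Programme timing.** "Within two weeks after the intake appointment at the SSA, the participatory supportive RTW program will start". Once the agency has the action plan: "Within four weeks, the agency has to offer at least two suitable workplaces". The case manager's evaluations follow six weeks and three months after placement.

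**The concern.** A QALY difference is the area under the between-arm utility difference over the year. With readings at 0, 6 and 12 months, the course between them has to be interpolated. If the difference bends inside a half-year, the interpolated area departs from the true one. The error cancels between arms only if both arms bend alike.

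The programme's opening steps fall in the first months, so the first half-year is where a bend is most plausible, and that half-year is described by its end points alone. At stake is the denominator of the cost-utility ratio. This is not a detail that an analysis plan could supply later: the plan can choose an interpolation rule, but it cannot restore readings that were never collected.

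**Working it through.** The article states no QALY figure, so there is none to reproduce. The check compares the three-point and five-point schedules.

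**1. General expression.** Assume linear interpolation and equal baselines (both are assumptions). Let d3, d6, d9 and d12 be the between-arm utility differences at each month, with time in years.

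- Three points: A3 = 0.50·d6 + 0.25·d12
- Five points: A5 = 0.25·(d3 + d6 + d9) + 0.125·d12
- A5 − A3 = 0.25·(d3 − d6/2) + 0.25·(d9 − (d6 + d12)/2)

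The two agree when the difference is linear within each half-year.

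**2. The sign depends on the course.** Illustrative differences at 3, 6, 9 and 12 months (assumed; the article gives none):

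| Assumed course | A5 | A3 |
|---|---|---|
| Reached by month 3 and held (0.10, 0.10, 0.10, 0.10) | 0.0875 | 0.0750 |
| Present at month 3, gone by month 6 (0.10, 0, 0, 0) | 0.0250 | 0 |
| Linear to month 6, then held (0.05, 0.10, 0.10, 0.10) | 0.0750 | 0.0750 |
| Onset only after month 3 (0, 0.10, 0.10, 0.10) | 0.0625 | 0.0750 |
| Early dip, then gain (−0.05, 0.05, 0.05, 0.05) | 0.0188 | 0.0375 |

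Three points understate in the first two rows, agree in the third and overstate in the last two.

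**3. A course tied to the article's own figures.** Assume exponential times to return to work and a utility difference proportional to the difference in the proportion returned. Let L be the day on which the arms begin to separate, with the control hazard in both arms before L. Then d(t) = exp(−λC·t) − exp(−λC·L − λI·(t − L)) for t > L, and 0 before.

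Two sets of inputs:

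- *Medians of the predecessor study* (Background, development of the intervention): 299 and 161 days. λC = ln 2/299 = 0.00232 and λI = ln 2/161 = 0.00431 per day.
- *Planning figures* (Sample size): hazard ratio 2.0 and 2/3 returned by 12 months, read as the pooled proportion. With x the control proportion not yet returned, 1 − (x + x²)/2 = 2/3 gives x = 0.457. So 54.3% return in the control arm and 79.1% in the intervention arm.

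Worked example (medians, L = 0): d3, d6, d9 and d12 are 0.1343, 0.1993, 0.2224 and 0.2213, and the exact area is 0.1706.

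- A3 = 0.50·0.1993 + 0.25·0.2213 = 0.155, about 9% low.
- A5 = 0.25·(0.1343 + 0.1993 + 0.2224) + 0.125·0.2213 = 0.167, about 2% low.

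Error against the exact area:

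| Separation starts | Medians: 3 points | Medians: 5 points | HR 2.0: 3 points | HR 2.0: 5 points |
|---|---|---|---|---|
| Day 0 | −9.2% | −2.3% | −8.9% | −2.2% |
| Day 45 | −0.1% | +1.3% | +0.1% | +1.3% |
| Day 60 | +2.6% | +1.1% | +2.7% | +1.1% |
| Day 75 | +4.9% | −0.1% | +5.1% | −0.1% |
| Day 90 | +6.8% | −2.8% | +6.9% | −2.7% |

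The three-point error runs from about −9% to +7%, and the five-point error from about −3% to +1%. At day 45 the three-point area happens to be the closer of the two, because its errors offset.

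**4. Precision.** With a common correlation of 0.4 to 0.7 between readings (assumed) and adjustment for baseline utility, moving from three to five points changes the variance of the area by −5% to +5%. The gain is therefore less interpolation error, not a narrower interval.

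**The case against.** The strongest reply is that nothing here is an error. A 0/6/12-month schedule contradicts no other statement, and the 4DSQ, SF-36 and ASE questionnaire follow the same one. That stands: this is a design choice with coarser resolution. The quarterly Tic-P does not make it inconsistent either, since the Tic-P measures health care use and the Euroqol a current state.

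A reader might go further and infer that early gains are bound to be understated, by 14% if reached by month 3 and held (0.75 recorded against 0.875 of the full difference), or lost entirely if gone by month 6. The documents do not support that. Those figures come from chosen shapes, and other shapes reverse the sign. The programme's own timeline also fits them poorly. Assessment, obstacle meetings, the brainstorm session and the written plan all precede the agency's four weeks. Two further agencies may then search, and placement with ongoing benefit can last up to three months. The predecessor programme's median time to sustainable return was 161 days. Utility could improve by routes other than return to work, but the article gives no course for that.

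The consequence is also confined. The stated objective concerns cost-effectiveness on time to sustainable return to work, and QALYs enter only the cost-utility part.

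What survives is narrower: the schedule is fixed in Table 1, the mailings already exist, and the missing readings cannot be recovered afterwards.

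**Conclusion.** The point holds as a possible, avoidable interpolation error in the QALY difference, with direction and size unknown. It vanishes if the between-arm utility difference is linear within each half-year. The range of roughly -9% to +7% for three points, against -3% to +1% for five, rests on several assumptions: linear interpolation, equal baselines, exponential return-to-work times, separation starting between day 0 and day 90, and utility proportional to return to work. It illustrates the order of magnitude and is not a forecast. The primary outcome, the cost data and the cost-effectiveness ratio on return to work are untouched. This is a worthwhile low-cost improvement, not a flaw that threatens the trial.

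**What to change.** Mark the Euroqol at T1 and T3 in Table 1, include it in the 3- and 9-month questionnaires already sent, and state that QALYs are computed from all five readings. The 4DSQ, SF-36, ASE questionnaire and WLQ can keep their present times, so that the intermediate questionnaires stay short. The cost is a few extra items in two existing mailings, slightly more response burden and a minor amendment. The telephone follow-up already planned for late or incomplete questionnaires would cover the added items. The sample size does not change.
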